# Evaluation of lived experience Peer Support intervention for mental health service consumers in Primary Care (PS-PC): study protocol for a stepped-wedge cluster randomised controlled trial

**DOI:** 10.1186/s13063-024-08165-y

**Published:** 2024-05-14

**Keywords:** Mental health, Primary care, Mental health services, Consumers, Peer workers, Lived experience workforce, Cluster-randomised trial

## Abstract

**Background:**

The demand for mental health services in Australia is substantial and has grown beyond the capacity of the current workforce. As a result, it is currently difficult for many to access secondary healthcare providers. Within the secondary healthcare sector, however, peer workers who have lived experience of managing mental health conditions have been increasingly employed to intentionally use their journey of recovery in supporting others living with mental health conditions and their communities. Currently, the presence of peer workers in primary care has been limited, despite the potential benefits of providing supports in conjunction with GPs and secondary healthcare providers.

**Methods:**

This stepped-wedge cluster randomised controlled trial (RCT) aims to evaluate a lived experience peer support intervention for accessing mental health care in primary care (PS-PC). Four medical practices across Australia will be randomly allocated to switch from control to intervention, until all practices are delivering the PS-PC intervention. The study will enrol 66 patients at each practice (total sample size of 264). Over a period of 3–4 months, 12 h of practical and emotional support provided by lived experience peer workers will be available to participants. Scale-based questionnaires will inform intervention efficacy in terms of mental health outcomes (e.g., self-efficacy) and other health outcomes (e.g., healthcare-related costs) over four time points. Other perspectives will be explored through scales completed by approximately 150 family members or carers (carer burden) and 16 peer workers (self-efficacy) pre- and post-intervention, and 20 medical practice staff members (attitudes toward peer workers) at the end of each study site’s involvement in the intervention. Interviews (*n* = 60) and six focus groups held toward the end of each study site’s involvement will further explore the views of participants, family members or carers, peer workers, and practice staff to better understand the efficacy and acceptability of the intervention.

**Discussion:**

This mixed-methods, multi-centre, stepped-wedge controlled study will be the first to evaluate the implementation of peer workers in the primary care mental health care sector.

**Trial registration:**

Australian New Zealand Clinical Trials Registry (ANZCTR) ACTRN12623001189617. Registered on 17 November 2023, https://www.anzctr.org.au/Trial/Registration/TrialReview.aspx?id=386715

**Supplementary Information:**

The online version contains supplementary material available at 10.1186/s13063-024-08165-y.

## Introduction

Mental health conditions account for 12% of fatal and non-fatal health burden in Australia, having the second highest non-fatal health burden after musculoskeletal disability [1]. A substantial number of Australians—21.5% of those aged 16–85 experienced difficulties in the past 12-month period or 42.9% across their lifespan [2]. Despite the mental health workforce capacity increasing by 6.5% in the period 2021–2022, availability has been surpassed by growing demand for mental health services [3]. This is especially so for priority groups (e.g., rural and remote) due to social determinants, geographical barriers, costs, and an even further reduced workforce capacity for providing services [3]. Difficulties accessing services has been further exacerbated by significant adverse events such as climate disasters and the COVID-19 pandemic [4, 5]. Economic costs associated with the figures are estimated to be between $43 and 70 billion per year [3]. Reports indicate that the current mental healthcare system requires wider reforms to provide equitable access to adequate support for the diverse needs of people living with mental health conditions [3, 6].

Australia has long emphasised a recovery-orientated approach in national and state/territory mental health plans and policy, aiming to go beyond an ‘illness’ model [7, 8]. This aligns with the desires of those living with mental health conditions to access mental health services earlier and to have more control over their own health [3, 8, 9]. Primary care services, including general practices and psychological services, play a pivotal role in offering this support and making referrals to specialised support [9]. However, many Australians face significant wait times and limited access (e.g., geographical, financial) to these services. This has led a considerable number of people seeking help at emergency departments in crisis or to slip through service gaps in a system increasingly focused on crisis management [3, 8, 10]. Therefore, there is an urgent need to enhance the delivery and quality of recovery-oriented mental health support through recovery-focused primary care interventions that give people living with mental health conditions a greater say in what supports are offered.

As a crucial step toward person-focused recovery-orientated care, peer support delivered by peer workers is increasingly being trialled worldwide [11–13]. Peer workers have lived experience (LE) of managing mental health conditions and are intentionally employed to leverage their experience of recovery to assist and support people living with mental health conditions and their network of informal supports [14]. Interaction between peer workers and others living with mental health conditions is founded on mutuality, equality, and reciprocity [13], with peer workers metaphorically ‘walking alongside’ the person living with mental health conditions whilst sharing their own recovery experience [7]. Further, peer workers connect people living with mental health conditions to services and community activities, aiding in customising services to their individual needs. LE peer support is multifaceted, involving positive self-disclosure, expansion of social networks, education, and advocacy. Ultimately, peer workers foster trust and engagement with services amongst people living with mental health conditions, concurrently reinforcing self-efficacy, connectedness, and resilience [7, 13].

Currently, peer workers are employed in various secondary and tertiary settings [13, 15], including emergency departments [16], crisis management [17], and community services [4]. A pilot study demonstrated the acceptability, feasibility, and effectiveness of peer support in preventing hospital admissions, lowering re-presentations, and reducing costs. This outcome led to the funding of a successful state-wide peer-supported post-hospital community service in Australia [18, 19]. Further, international randomised controlled trials (RCTs) [20, 21] and systematic reviews [22, 23] have confirmed the effectiveness of peer support in acute care settings through demonstrating improved psychosocial and care outcomes. Despite existing evidence suggesting that peer support yields more responsive, safe, effective, and person-centred care [22], peer workers remain absent from the primary care workforce in Australia and worldwide.

General practitioners (GPs) are vital to primary mental health care as they act as the principal referrers for supports. Approximately 5 million Australians (25%), including 2.3 million with mild and 1.1 million living with moderately severe mental health conditions, seek support from GPs annually [24]. This level of engagement suggests an opportunity to supply additional supports at the primary care level which are available, accessible, and recovery focused. To address the challenges surrounding the provision of mental health care in the primary setting, we are trialling the implementation of a lived experience Peer Support intervention for those accessing mental health care in Primary Care (PS-PC). The PS-PC intervention will be offered in four general practices—three regional and one remote—with the intention to empower those living with mental health conditions to improve their self-efficacy, personal recovery, access to services, and quality of life.

## Objectives

The primary objective of this study is to understand the efficacy of the PS-PC in enhancing the self-efficacy (i.e., a person’s belief in their ability to manage their mental health and recovery) of those who are accessing mental health services at a primary care level (i.e., mental health service consumers). A secondary objective is to assess the feasibility of peer worker support in the general practice setting and identify barriers to implementation.

## Methods

### Study design and setting

This mixed-method, multi-site, stepped-wedge cluster RCT trial will evaluate the PS-PC in the primary care setting across four Australian practices (study sites). The PS-PC intervention was designed using the Experience Based Co-Design (EBCD) Framework, with a focus on the combined experiences and knowledge of those who provide and receive mental healthcare [25]. The experiences of the providers and recipients of care were considered in the co-design process through:A Project Reference Group (PRG) consisting of all investigators involved in the project. The PRG is responsible for monitoring the research activities within the project, including the management of challenges at the project management level.A Stakeholder Reference Group (SRG) consisting of individuals or organisations in the community that have a stake in the outcomes of the PS-PC project, including mental healthcare consumers. The SRG is responsible for advising and overseeing all project activities to ensure that the experience of community stakeholders was included across the project.Semi-structured interviews held with Australian mental healthcare consumers, family/carers, and peer workers to understand the experiences of those engaged with mental health care services.Three workshops (one at each study site 1–3), held with practice staff, mental healthcare consumers from the community, sector specialists, peer workers, and CMO representatives. Workshops were held on-site, but virtual attendance via Microsoft Teams was available to be inclusive for all invitees. Workshops were intended to foster relationships between different groups, to introduce the peer role to those who were unfamiliar, and to understand how to best tailor the intervention to each study site.Semi-structured interviews were held with GPs, practice managers, nurses, and reception staff at study sites 1–3 to understand the experiences of those who provide mental healthcare services at the primary care level and how peer workers might be accommodated in this space.

Guidance in constructing the intervention came from these sources through thematic analysis (deductive and inductive), engagement with the SRG and PRG, and ongoing communication between the research officer, practice managers, and peer coordinators. See Additional File 1 for more detail.

Design and selection of planned evaluation methods followed the Consolidated Framework for Implementation Research (CFIR) [26] and RE-AIM (Reach, Effectiveness, Adoption, Implementation, Maintenance) Framework. A study diagram based on CONSORT demonstrating the planned reporting of the intervention can be seen in Fig. 1.

**Fig. 1 Fig1:**
[figure not shown]
Study diagram (based on CONSORT [27]) for flow of participants by study site

The study will take place in four general practice clinics across rural and regional areas of Australia. Peer workers will be employed by community-managed organisations (CMOs) that are able to provide services to these areas. The locations of participating sites is available on the trial registration page [28]. Approval for the study has been granted by the Flinders University Human Research Ethics Committee (#6386). The SPIRIT reporting guidelines (see Additional File 2) were used in the development of this protocol [27].

## Sample size

The sample size calculation (*n* = 264 participants; 66 per practice) is based on the primary outcome of the self-efficacy score from an RCT assessing the effectiveness of peer support for mental health outpatients in Germany [29]. Adjusted scores significantly improved by an average of 1.77 points (95% CI 0.02–3.53) in the peer support group compared to usual care (mean score = 24.3, pooled SD = 7.2) in the 6-month follow-up. As this study is based on 9-month follow-up, the upper confidence level of the improved score will be used. Assuming a 10% attrition rate, we will need to recruit 66 participants per practice with a total of 264 participants. This achieves at least 80% power to detect a difference of mean self-efficacy score of 3.53 points. A power and sample-size analysis for hypothesis test from Stata version 16.1 was used to calculate the sample size*.* The test statistic used is the one-sided Wald *Z*-test and the significance level of the test is 0.05. Assuming heterogeneity amongst practices and substantial differences (i.e., minimal resemblance) in participants at each site, the responses of participants will not be significantly influenced by their enrolment at a particular practice. As such, the ICC is 0.01.

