## Primary outcome measures

The primary outcome will be change in a person’s self-efficacy measured by the GSE [32]. The GSE is a reliable (*α* = 0.76 to 0.90), validated, ten-item unidimensional self-report scale used to assess self-efficacy within general adult populations. The scale conceptualises self-efficacy as a person’s perceived ability to cope and adapt in the face of both daily hassles and more stressful life events. Respondents indicate how much a given item applies to them from 1 (not at all true) to 4 (exactly true), with total possible scores of 10–40 (higher scores indicate greater self-efficacy). The scale was originally designed to assess change occurring over the course of a trial and is also used in CMO contexts as an indicator of client well-being. This tool will be used to inform intervention efficacy for participants at baseline, 3 months post-baseline, 6 months post-baseline, and 9 months post baseline. For all measures taken at multiple time points, the comparison between care as usual (baseline) and post-intervention (3 months post-baseline) will be of primary importance, whilst following time points will inform the longevity of any intervention-related effects.

All baseline measures, including the GSE, will be administered as a questionnaire by a practice nurse following screening and consent procedures. During the final session of peer support, the peer worker will assist the participant with completing the 3-month post-baseline measures. All further follow-up measures will be administered as a questionnaire either through REDCap or a telephone call from study staff depending on participant preference.

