## Statistical methods

Independent sample *t*-test and standard Chi-square test for association with continuity correction will compare participant characteristics during usual care with those during mid- and post-intervention. Multivariate multilevel mixed-effects models will be used to examine changes in outcome measures between pre-intervention baseline and post-intervention follow-up over time (6, 12, and 18 months) including interactions between pre-intervention baseline and post-intervention follow-up over time. The comparison between care as usual (baseline) and post-intervention (3-months post-baseline) will be of primary importance, whilst subsequent time points will inform the longevity of any intervention-related effects. This analytical strategy is selected due to the hierarchical nature of the data, where participants are nested within practices. Linear models will be used for continuous outcomes (i.e., GSE, K10, RAS-DS, YES, EQ-5D-5L, TFA) and logit models for binary outcomes (e.g., demographics, diagnosis, etc.). The two-sided test will be performed for all analyses, 95% confidence interval reported, and level of significance set at *p* < 0.05. All analyses will be performed using Stata software version 16.1 and R version 4.1.1. Responses on the EQ-5D-5L integrated with survival curves will be integrated estimate quality adjusted life years using the quality-adjusted survival analysis method. Participant self-reported service use during usual care will be compared with those during and post-intervention to determine within-trial incremental costs and trial effectiveness. Where there is missing data, intention-to-treat protocol will be followed for all participants who receive peer support, where baseline information is available. If there is a significant amount of missing data (missing at random), multiple imputation will be used.

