## Discussion

This multi-centre, stepped-wedge controlled study will provide peer support to people seeking care for mental health conditions within general practice. This will be achieved by connecting participants with peer workers, with the intention of improving access to relevant supports, improved self-efficacy in navigating the mental healthcare system, taking control of their own health needs, mitigating psychological distress, and promoting personal recovery. Aligned with the EBCD ethos, the ongoing engagement with various key stakeholder groups will provide opportunities for continuous improvement, monitoring, and maintenance of the intervention and its outcomes.

The study may also further benefit the family members and carers involved in the participant’s care by reducing the amount of support they provide. In addition, peer workers may experience increased self-efficacy, along with greater understanding of general practice, from providing support through this intervention. Furthermore, practice staff may benefit from a greater understanding and acceptance of the peer worker role through exposure to peer worker care processes. The results of this study will provide greater insight into the role of for peer workers within the primary care setting. Finally, findings around the cost–benefit of the PS-PC will inform economic feasibility of peer workers in primary care settings. There is a compelling need for a comprehensive trial of peer support at the primary level [3]. If positive, the study may provide information to support the inclusion of primary mental health peer workers within the Medicare Benefits Schedule. If negative, this adequately powered study will help to inform practice within CMOs and clinical practice. Overall, this study will provide opportunities to extend the role of peer workers throughout the healthcare system.

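### Nine-month follow-up does not justify sizing on 3.53 points, the reference trial's upper confidence limit; at its estimate of 1.77 the stated one-sided calculation has about 35% power (about 24% two-sided)

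*Protocol article*

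**What the plan says.** The Sample size section of the protocol article reports from the reference trial: "Adjusted scores significantly improved by an average of 1.77 points (95% CI 0.02–3.53) in the peer support group". The comparator was usual care ("mean score = 24.3, pooled SD = 7.2) in the 6-month follow-up"). The target is then moved from the estimate to its upper limit: "As this study is based on 9-month follow-up, the upper confidence level of the improved score will be used". No other reason is given, and 3.53 is not presented as a minimal important difference. With an ICC of 0.01, 10% attrition and 66 participants in each of four practices (264 in total), the section concludes: "This achieves at least 80% power to detect a difference of mean self-efficacy score of 3.53 points". On the test it says: "The test statistic used is the one-sided Wald *Z*-test and the significance level of the test is 0.05".

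Three statements elsewhere bear on this:

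- Primary outcome measures: "the comparison between care as usual (baseline) and post-intervention (3 months post-baseline) will be of primary importance". Statistical methods repeats this, and both sections leave later time points to show how long any effect lasts.
- Statistical methods: "The two-sided test will be performed for all analyses, 95% confidence interval reported, and level of significance set at" p < 0.05.
- Discussion: "If negative, this adequately powered study will help to inform practice within CMOs and clinical practice".

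**The concern.** The target is twice the effect that the cited evidence estimates, and the reason given for doubling it fails in two ways.

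First, the width of a confidence interval reflects how many people the reference trial studied and how variable they were. It carries no information on how the effect changes between month 6 and month 9.

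Second, the reason concerns a time point that is not the primary one. The primary contrast is at 3 months, earlier than the reference trial's 6 months. If effects grow with follow-up, as the Sample size section implies, the 3-month effect should be no larger than the 6-month one.

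What is at stake is how a non-significant result will be understood. The Discussion describes the study as adequately powered without saying for what effect. A reader would not learn that this rests on 3.53 points, or how far power falls if the true effect is nearer the reference estimate.

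**Working it through.** **Inputs.** From Sample size: target 3.53, reference estimate 1.77, SD 7.2, ICC 0.01, four practices, 66 per practice, 10% attrition, one-sided α = 0.05. From Statistical methods: two-sided α = 0.05. Assumed: five periods with one practice switching per step, because the article does not state the number of periods.

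**Step 1. Reproduce the stated figure.** The Hussey–Hughes variance for the between-condition effect, with I = 4 practices, T = 5 periods and m participants per practice-period, is

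Var = I·s²·(s² + T·t²) / [(I·U − W)·s² + (U² + I·T·U − T·W − I·V)·t²]

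- s² = 0.99 × 7.2² / m. At m = 12 this is 51.32 / 12 = 4.277.
- t² = 0.01 × 7.2² = 0.518.
- For this layout U = 4 + 3 + 2 + 1 = 10, W = 0 + 1 + 4 + 9 + 16 = 30 and V = 16 + 9 + 4 + 1 = 30.
- Numerator: 4 × 4.277 × (4.277 + 2.592) = 117.5.
- Denominator: 10 × 4.277 + 30 × 0.518 = 58.3.
- SE = √(117.5 / 58.3) = 1.419.

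One-sided power at 3.53 is Φ(3.53/1.419 − 1.645) = Φ(0.842) = 80.0%. The smallest m that reaches 80% is 12, so 5 × 12 = 60 per practice. Multiplying by 1.1 for attrition gives 66, and 4 × 66 = 264, the stated total. (Dividing by 0.9 would give 67 and 268.)

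**Step 2. Same SE, other effect and other test.**

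| True effect | One-sided (Sample size) | Two-sided (Statistical methods) |
|---|---|---|
| 3.53 (3.53/7.2 = 0.49 SD) | Φ(0.842) = 80.0% | Φ(2.487 − 1.960) = 70.1% |
| 1.77 (1.77/7.2 = 0.25 SD) | Φ(1.247 − 1.645) = 34.5% | Φ(1.247 − 1.960) = 23.8% |

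**Step 3. Dependence on the assumed layout.** Any normal-theory calculation with exactly 80% one-sided power at 3.53 has a shift of 1.645 + 0.842 = 2.486 there. At 1.77 the shift is 2.486 × 1.77/3.53 = 1.247, which gives the same 34.5% and 23.8%. Other readings at 1.77:

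- Five-period wedge with 59.4 to 66 analysed per practice: 34.3–36.5% one-sided, 23.6–25.5% two-sided.
- The stated 80% taken as two-sided: 28.9% two-sided.
- Parallel design, two practices against two, 60 per practice: design effect 1 + 59 × 0.01 = 1.59, SE = 7.2 × √(2 × 1.59/120) = 1.172, power 44.6% one-sided and 32.6% two-sided. At 3.53 this reading gives 91.4% and 85.4%, so it does not reproduce 80%.
- The same parallel design with the ICC dropped, contrary to the plan: 60.2% and 47.8%.

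**Step 4. Precision.** The 95% interval half-width is 1.96 × 1.419 = 2.78 points. An estimate of exactly zero would have an interval of about −2.8 to 2.8, which excludes 3.53 but contains 1.77.

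**The case against.** The strongest reply is that the contrast described as primary compares baseline with 3 months in the same people, so a between-condition power figure is not its power. This stands. With SD 7.2, 264 × 0.9 ≈ 238 completers and a simple within-person change, the SE is 7.2 × √(2(1 − r)/238). Two-sided power at 1.77 is then about 76%, 89% and 97% for within-person correlations r of 0, 0.3 and 0.5, which are assumed values. This simple version ignores period adjustment and varying practice effects, so it does not show that the trial is well powered. It does mean that a reader who took 24% as the power of the 3-month change would be inferring more than the documents allow. The 24% and 35% belong to the between-condition stepped-wedge effect.

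Other replies:

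- The plan says at least 80%, and five periods is an assumption. True, but Step 3 shows that the figures at 1.77 follow from 80% at 3.53 whatever the layout.
- The effect might peak when peer support ends, near 3 months. It might, but the protocol does not argue this, and it would not make a confidence limit the right target.
- An optimistic target is a permitted choice. Agreed; the fault is the reason given and the unqualified power claim.

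Three stronger inferences should be resisted:

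- That a null result would most likely be a missed effect. This needs a prior for the true effect, and the reference interval reaches down to 0.02. What can be said is conditional: if the true effect is 1.77, the two-sided between-condition test misses it about 76% of the time (100 − 23.8).
- That the protocol binds itself to reading a null as absence of benefit. The Discussion sentence says only that the result will help inform practice.
- That the reference interval leaves a 2.5% chance of an effect of 3.53 or more. That treats a confidence interval as a probability distribution for the effect.

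**Conclusion.** The point holds. The stated reason for using 3.53 is wrong on the article's own text: a confidence limit does not measure growth of effect, and the primary comparison is at 3 months, not 9.

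On the reproduced calculation (SD 7.2, ICC 0.01, four practices, five periods assumed, 60 analysed per practice), power at the reference estimate of 1.77 is about 35% with the stated one-sided test and about 24% with the planned two-sided test. At 3.53 it is 80% and about 70%. The more favourable parallel-cluster reading gives about 45% and 33% at 1.77. The claim of adequate power is thus supported only for an effect twice the reference estimate.

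The drop from the one-sided to the two-sided column is a separate defect, the mismatch between Sample size and Statistical methods. It should not be attributed to the choice of target: the target alone takes the stated one-sided power from 80% to about 35%.

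The documents give no minimal important difference. They therefore do not support treating 1.77, one trial's estimate, as the smallest useful effect.

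**What to change.** Keep 264 participants and make these changes of wording:

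1. In Sample size, delete the 9-month justification. State openly that 3.53 is an optimistic target, or justify it on independent grounds.
2. Report power for the between-condition stepped-wedge effect under the planned two-sided test at both 1.77 and 3.53 (about 24% and 70% on the assumptions above). State the model and the number of periods, and replace these figures if the actual layout differs. Do not label them as the power of the within-person change from baseline to 3 months.
3. In the Discussion, replace the claim of adequate power with a statement that power is adequate only for large effects. Add that a non-significant result will be interpreted from its 95% confidence interval, with an expected half-width of about 2.8 points on the stated assumptions. Do not set 1.77 as a fixed threshold for usefulness.

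The cost is a less favourable published power figure. No extra recruitment or change of design is needed, which matters because the Trial status section says recruitment has begun.

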## Randomisation

The four practices will be randomly allocated by the study statistician to receive the standardised PS-PC intervention until all four sites have implemented it. Timing of allocation will depend on the relative needs of the practices and peer worker providers (e.g., staffing, leave arrangements, time of year). At the initialisation of each wedge, staff leaders at the relevant practice site will champion the practical implementation of the PS-PC, beginning with recruitment strategies. All participants will receive usual care, plus the addition of peer support when their study site switches to the PS-PC intervention. Due to the trial’s specific nature, neither randomisation nor blinding of participants will take place. Participants have the freedom to withdraw from the intervention at any time upon their request.

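### The stated 80% power belongs to a peer-support versus usual-care difference, not to the baseline-to-3-month change that the protocol makes primary

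*Protocol article*

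**What the plan says.** The Sample size section of the protocol article takes its effect from a parallel-group trial of peer support. The adjusted difference was 1.77 points on the self-efficacy scale (95% CI 0.02 to 3.53) "in the peer support group compared to usual care (mean score = 24.3, pooled SD = 7.2"). The upper confidence limit becomes the target, with an ICC of 0.01 and a one-sided Wald Z-test at 0.05. The result is stated as follows: "Assuming a 10% attrition rate", "we will need to recruit 66 participants per practice with a total of 264 participants", and "This achieves at least 80% power to detect a difference of mean self-efficacy score of 3.53 points". No correlation between repeated scores of one person is given.

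The Abstract describes the design: "Four medical practices across Australia will be randomly allocated to switch from control to intervention". Under Randomisation: "At the initialisation of each wedge, staff leaders at the relevant practice site will champion the practical implementation of the PS-PC, beginning with recruitment strategies". Under Primary outcome measures: "During the final session of peer support, the peer worker will assist the participant with completing the 3-month post-baseline measures". Table 1 lists the participant self-efficacy score at enrolment or baseline and at 3, 6 and 9 months after baseline. Under Statistical methods: "The comparison between care as usual (baseline) and post-intervention (3-months post-baseline) will be of primary importance". The Discussion then calls the study adequately powered when it explains what a negative result would mean.

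**The concern.** Power is a property of a particular contrast with a particular standard error. The sample-size paragraph describes a contrast between two groups of people, one scored after peer support and one scored under usual care. The outcome and analysis sections describe a contrast within each person: own baseline, which the protocol labels usual care, against a score taken in the last peer-support session. These are different quantities. The first compares the intervention with its absence. The second also contains whatever would have changed over three months without it, and its standard error depends on the within-person correlation.

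At stake is how a reader interprets the result. The Discussion offers the power statement as the reason a negative finding would be informative, and it links a positive one to public funding of peer workers. Neither inference is supported by a power figure calculated for another comparison.

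**Working it through.** **Inputs from the Sample size section.** Target 3.53 points, SD 7.2, ICC 0.01, one-sided 0.05, 10% attrition, 66 recruited per practice, 264 in total. Four practices switching one at a time imply 5 periods; the number of periods is not printed.

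**Step 1: reproduce the stated figure.** I used the Hussey–Hughes variance for a cross-sectional stepped wedge with I = 4 practices, T = 5 periods and m = 12 different people per practice-period.

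- Total variance 7.2² = 51.84; between practices τ² = 0.01 × 51.84 = 0.5184; within practices 51.3216. Cell-mean variance σ² = 51.3216/12 = 4.2768.
- Design sums: U = 10, W = 30, V = 30.
- Var = Iσ²(σ² + Tτ²) / [(IU − W)σ² + (U² + ITU − TW − IV)τ²]
- = 4 × 4.2768 × 6.8688 / [10 × 4.2768 + 30 × 0.5184] = 117.506/58.320 = 2.0148, so SE = 1.4195.
- Power = Φ(3.53/1.4195 − 1.645) = Φ(0.842) = 80.0%.

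With 11 per cell the power is 77.3%, so 12 is the smallest number that reaches 80%. Then 12 × 5 = 60 per practice, 60 × 1.1 = 66, and 4 × 66 = 264, exactly as printed. Two-arm cluster layouts with 60 per practice do not match: two practices against two gives 91.4% and would need only 35 per practice; one against three gives 83.2% and would need 52. Of the variants tried, only the stepped wedge returns both the 80% and the 66.

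**Step 2: what that layout requires.** Of its 20 practice-periods, 10 come before the switch. So 10 × 12 = 120 of 240 people would be scored under usual care, in practices that have not yet switched.

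**Step 3: what the text schedules.** Recruitment is the first step of implementation at a practice's own wedge. The 3-month score is taken in the final peer-support session, and the 6- and 9-month scores come later. The text lists no follow-up score under usual care. The primary contrast is own baseline against 3 months.

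**Step 4: precision of the contrast as written.** Completers: 264 × 0.9 = 237.6, taken as 237. SE = 7.2 × √(2(1 − r)/237). The protocol gives no r, so 0.3 to 0.7 is an assumption.

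| r | SE | Two-sided power, 3.53 points | Two-sided power, 1.77 points |
|---|---|---|---|
| 0.3 | 0.553 | above 99.9% | 89.2% |
| 0.5 | 0.468 | above 99.9% | 96.6% |
| 0.7 | 0.362 | above 99.9% | 99.8% |

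The SE in Step 1 is about 2.6 to 3.9 times these values (1.4195/0.553 and 1.4195/0.362). The table gives power to detect a change over time from any cause.

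**Step 5: could the written schedule still give a controlled estimate?** Possibly, if baselines at later practices coincide in calendar time with follow-up at earlier ones. I fitted the Step 1 variance model (fixed period effects, random practice intercept) with 66 × 0.9 = 59.4 people per practice, treating each practice as enrolled at one time point.

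- Steps of 3 months, baseline and 3-month scores only: estimable, SE 0.83 (r = 0) to 0.63 (r = 0.7).
- Steps of 4 or 6 months, the same two scores: not identified, because no calendar point is shared in a useful way.
- Steps of 6 months, all four scores: estimable, SE 0.82 to 0.52.

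The step length is not stated, so none of these can be called the trial's precision.

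**The case against.** The strongest reply is that nothing is miscalculated: the 80% and the 264 reproduce, and a stepped-wedge calculation suits a declared stepped-wedge design. That stands. The fault is a mismatch between the calculation and the comparison later called primary.

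A second reply is that the text hints at a phase before the switch. Participants are said to gain peer support when their site switches, Table 1 allows an enrolment time point, and service use under usual care is to be compared with later use. The figures showing participant flow and the assessment schedule are not available here. This is a fair caution against saying that pre-switch enrolment is ruled out. But none of these passages adds a self-efficacy follow-up score under usual care, and Table 1 gives enrolment and baseline as alternatives for one starting score. The primary comparison is also stated in words, not left to a figure.

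A third reply is that the sample is more than large enough for the written contrast. That is true for an uncontrolled change, and it does not rescue a claim about peer support against usual care.

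A reader might also go further and infer that the trial has no usual-care observations, so that an effect against usual care cannot be estimated. The document does not support that. Every baseline counts as a usual-care score, practices start at different times, and under some step lengths later baselines make the effect estimable.

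**Conclusion.** The point holds as a mismatch, and it needs correcting. The printed 80% for 3.53 points is power for a controlled difference with one score per person (SE about 1.42). The comparison the protocol calls primary is a within-person change with SE of about 0.55 to 0.36 and nominal power above 99.9% for the same 3.53 points. The higher figure must not be read as power against usual care.

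Two assumptions carry the numbers. The layout of 5 periods with 12 per practice-period is inferred from an exact match, so the 120 of 240 is not a printed figure. The correlation of 0.3 to 0.7 is mine. The main conclusion needs neither: the power paragraph refers to people under peer support against people under usual care, and the analysis refers to each person's own change.

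The text does not show that the trial is underpowered or that a controlled effect is beyond estimation. Whether one is estimable, and how precisely, depends on step lengths that the protocol does not state. The one-sided test, the ICC and the choice of the upper confidence limit are separate matters.

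**What to change.** In the Sample size section:

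1. State that the 80% refers to a peer-support versus usual-care difference, and that it requires participants whose self-efficacy outcome is scored under usual care in practices that have not yet switched. Give the periods and numbers per practice-period used. If such scores are planned, say where in the schedule they fall.
2. Recompute and restate power for the comparison and model actually used under Primary outcome measures and Statistical methods, with the assumed within-person correlation and step length.
3. If baseline versus 3 months stays primary, say plainly that its power is for an uncontrolled change over time and not for an effect against usual care.

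In the Discussion, qualify the statement that the study is adequately powered so that it names the comparison it applies to.

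The cost is a rewritten paragraph, one sentence of the Discussion and a short recalculation, with no extra participants. The downside is that, unless usual-care outcome scores are in fact scheduled, the trial gives up its 80% claim for the controlled comparison.
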